# Effect of post-extubation high-flow nasal cannula combined with respiratory training versus conventional oxygen therapy on postoperative pulmonary complications in patients after major abdominal surgery: protocol for a single-centre randomized controlled trial

**DOI:** 10.1186/s13063-023-07311-2

**Published:** 2023-06-13

**Keywords:** Postoperative pulmonary complications, High-flow nasal cannula, Conventional oxygen therapy, Randomized controlled trial, Major upper abdominal surgery

## Abstract

**Background:**

Nearly 234 million patients undergo surgery each year, and 1.3 million among them develop complications. Patients undergoing major upper abdominal surgery (operation time > 2 h) have a really high incidence of postoperative pulmonary complications (PPCs). The occurrence of PPCs seriously affects the outcomes of patients. High-flow nasal cannula (HFNC) is as effective as noninvasive ventilation (NIV) in preventing postoperative hypoxaemia and respiratory failure. Respiratory training using positive expiratory pressure (PEP) Acapella (Choice) has been shown to help patients with rapid recovery from postoperative atelectasis. However, no relevant randomized controlled studies have been conducted to clarify the effect of HFNC combined with respiratory training in the prevention of PPCs. This study aims to investigate whether the use of HFNC combined with respiratory training could reduce the incidence of PPCs within 7 days after major upper abdominal surgery compared to that with conventional oxygen therapy (COT).

**Methods:**

This is a randomized controlled single-centre trial. A total of 328 patients who undergo major abdominal surgery will be included. Subjects who fulfil the eligible criteria will be randomly assigned into the combination treatment group (Group A) or COT group (Group B) after extubation. The interventions will begin within 30 min of extubation. Patients in Group A will receive HFNC for at least 48 h and respiratory training three times a day for at least 72 h. Patients in Group B will receive oxygen therapy through a nasal catheter or mask for at least 48 h. Our primary endpoint is the incidence of PPCs within 7 days, and the secondary outcome measures include 28-day mortality, reintubation rate, length of hospital stay, and all-cause mortality within 1 year.

**Discussion:**

This trial would help provide evidence on the effectivity of applying HFNC combined with respiratory training for the prevention of PPCs in patients undergoing major upper abdominal surgery. The objective of this study is to determine the optimal treatment approach to improve the prognosis of patients undergoing surgery.

**Trial registration:**

ChiCTR2100047146. Registered on 8 June 2021. Retrospectively registered.

**Supplementary Information:**

The online version contains supplementary material available at 10.1186/s13063-023-07311-2.

## Administrative information

Note: The numbers in curly brackets in this protocol refer to SPIRIT checklist item numbers. The order of the items has been modified to group similar items (see http://www.equator-network.org/reporting-guidelines/spirit-2013-statement-defining-standard-protocol-items-for-clinical-trials/).

## Introduction

### Background and rationale {6a}

Nearly 234 million patients undergo surgery every year, among whom 1.3 million patients experience complications [1]. Postoperative pulmonary complications (PPCs), including hypoxemia, pneumonia, respiratory failure, atelectasis are more common than cardiovascular complications following surgery [2, 3]. Such complications have high incidence ranging from 6 to 80% and are a leading cause of poor surgical outcomes [4]. Studies estimate that nearly one million PPCs occurred annually in the United States, resulting in 46,200 deaths and 480,000 additional hospital days [5]. Despite the intraoperative use of protective ventilation practices, Ana et al. [6] found PPCs more commonly in patients with surgery lasting more than 2 h and an American Society of Anaesthesiologists (ASA) status 3. Most PPCs occurred within 7 days of surgery. Even mild PPCs can significantly affect the postoperative mortality and therefore deserve close attention and intervention in clinical practice.

The incidence of PPCs is up to 40% in patients with an ASA status 3, and thoracic or upper abdominal surgeries [7]. The pathogenesis of PPCS includes a decreased functional residual capacity (FRC), atelectasis, ineffective cough and abnormal respiratory control [8, 9]. Effective prevention of PPCs is strongly associated with a shorter hospital stay and decreased mortality. Postoperative factors including respiratory support, breathing training, and physical therapy increasingly affect the incidence of PPCs. Current respiratory support methods include noninvasive ventilation (NIV), high-flow nasal cannula (HFNC), and conventional oxygen therapy (COT). NIV is effective in preventing and treating respiratory failure and reducing the rate of postoperative tracheal reintubation in different populations [10, 11]. However, recent research shows that the routine prophylactic use of NIV after major abdominal surgery does not reduce the incidence of PPCs [12]. Furthermore, some patients cannot effectively cooperate and tolerate NIV. In addition, the use of NIV after abdominal surgery may increase the risk of gastrointestinal fistulas. Therefore, routine use of prophylactic post-operative NIV is not recommended.

HFNC uses heated humidification, high flow (up to 60L/min), and a high oxygen concentration (up to 100%). At high flow rates, HFNC is believed to increase positive end-expiratory pressure by 4–6 cmH_2_O [13]. Besides patients feel more comfortable using HFNC than with NIV or COT. Studies have shown that HFNC is not inferior to NIV and COT in populations at high risk for PPCs in preventing hypoxaemia and respiratory failure [14]. Frat et al. compared the effects of HFNC, COT, and NIV in hypoxic respiratory failure and found that the 90-day mortality rate was lowest in the HFNC group, although no significant difference was observed in the reintubation rate [15]. Compared with COT, HFNC provided better oxygenation, better comfort, and lower reintubation rate at the same oxygen concentration [16]. Recent study indicates the use of HFNC did not reduce the rate of reintubation in comparison to COT; however, HFNC yielded less frequent use of rescue NIV [17]. HFNC is not inferior to NIV in preventing reintubation and post-extubation respiratory failure in populations at high risk of reintubation [18]. Recent guidelines of the European Respiratory Society suggest using either HFNC or NIV in postoperative patients at high risk of respiratory complications. Additionally, they also suggest using either COT or HFNC in postoperative patients at low risk of respiratory complications [19].

In addition, postoperative diaphragmatic dysfunction is also the pathophysiological basis of PPCs. Preoperative inspiratory training is believed to reduce the occurrence of PPCs after major thoracic and abdominal operations [20]. The Acapella vibrating ventilation therapy produces a positive pressure of 5–15 cmH_2_O at the end of the breath to maintain lung expansion. It can promote sputum excretion, strengthen respiratory muscle, and reduce the incidence of alveolar collapse, pneumonia, and hypoxaemia. Studies have shown that this therapeutic system is as effective as other airway clearance techniques in improving respiratory symptoms, expectoration, lung capacity, and health-related quality of life [21]. However, previous studies have shown that the routine use of incentive spirometry for breathing training after major upper abdominal surgery did not reduce the incidence of PPCs [22, 23]. Well-designed clinical trials are urgently required for further validation.

These two interventions have theoretical benefits for the prevention of PPCs. However, previous clinical studies have shown that neither HFNC nor breathing training after surgery shows a significant difference in the occurrence of PPCs. In our clinical practice, we observed that patients at high risk for PPCs recovered faster using HFNC combined with respiratory training (positive expiratory pressure [PEP] Acapella Choice). Therefore, a pilot trial of 12 cases of the combined use of HFNC and Acapella breathing training was conducted. The incidence rate of PPCs was 50% (3/6) in the COT group, while the incidence of PPCs was 16.7% (1/6) and the diaphragm function recovered faster in the combination treatment group. To date, no randomized controlled trials have verified the role of HFNC combined with respiratory training in preventing PPCs. We believe that this randomized controlled study will provide new evidence for the prevention of PPCs and improve the long-term prognosis.

### Objectives {7}

Primary objective: To reduce the incidence of PPCs within 7 days of surgery compared with routine use of COT and apply these findings to clinical practice.

Secondary objective: To investigate whether HFNC combined with respiratory training can improve postoperative outcomes of patients, such as reducing 28-day mortality, 1-year all-cause mortality, reintubation rates, and length of hospital stay after major upper abdominal surgery.

### Trial design {8}

The study is a parallel, single-blind, randomized controlled clinical trial (RCT). Patients who fulfil the eligibility criteria and signed the informed consent will be randomly assigned to either the combination treatment group (Group A) or the COT group (Group B) in a 1:1 ratio. Periodic evaluation will be made daily within 1 week, at discharge, the 28^th^ day, and 1 year after the surgery. We hypothesize that Group A would have a lower incidence of PPCs compared to Group B.

## Methods: participants, interventions, and outcomes

### Study setting {9}

Patients who undergo elective abdominal surgery (operation time > 2 h) at the Seventh Affiliated Hospital, Sun Yat-sen University, will be recruited and will be considered for inclusion if they meet the criteria as defined below.

### Eligibility criteria {10}

#### Inclusion criteria

age ≥ 18 years, (2) surgery time ≥ 2 h, (3) abdominal surgical site, and (4) BMI ≤ 35 kg/m[2] (normal, mild obesity, excluding moderate to severe obesity).

#### Exclusion criteria

Endotracheal intubation not successfully removed within 24 h after surgery;Obstructive sleep apnoea syndrome (OSAHS);Patients with haemodynamic instability (defined as the need for a norepinephrine dose > 0.5 ug/ kg/min or dopamine > 10ug / kg/min to maintain mean arterial pressure [MAP] ≥ 65 mmHg);Contraindications for the use of the PEP Acapella (Choice) including: inability to follow verbal instructions, active haemoptysis, oesophageal surgery, untreated pneumothorax, and haemodynamic instability.Significant abnormal preoperative chest radiograph or chest CT affecting the identification of PPCs;Abnormal preoperative chest X-ray or CT scan, which affects the discrimination of PPCs;Preoperative impaired consciousness or mental illness (Glasgow score ≤ 14);Participation in other clinical studies;Pregnant woman; and Informed consent not obtained.

### Who will take informed consent? {26a}

All patients undergoing upper abdominal surgery were initially assessed for eligibility. For elective surgery with an expected duration over than 2 h, the study group will obtain informed consent prior to surgery. Furthermore, for emergency surgery longer than 2 h, an informed consent will be signed after surgery with authorized surrogates. The specific situation of the trial will be explained in detail after the patient has regained consciousness. The participants can communicate with the study group or doctor for any remaining questions at any time.

### Additional consent provisions for collection and use of participant data and biological specimens {26b}

This trial does not involve collecting biological specimens.

## Interventions

### Explanation for the choice of comparators {6b}

The COT group received oxygen by nasal catheter or mask for at least 48 h after extubation.

### Intervention description {11a}

In both groups, implementation of the intervention will start within 30 min of extubation. Postoperative extubation procedures will be performed according to the ATS/ACPP clinical practice guidelines for mechanical ventilation withdrawal. Pain management will be administered to maintain a VAS score of < 3. Decisions regarding other treatment and monitoring will be conducted based on routine clinical practice.

#### Combination treatment group (Group A)

After extubation, patients will receive HFNC therapy for at least 48 h and respiratory training three times a day for at least 3 days.

#### HFNC therapy

Patients will receive oxygen therapy through HFNC. Initial parameters will be set as follows: flow 50L/min, FiO2 100%, T 37.0℃. Then downgrade FiO_2_ to the lowest value to maintain SPO_2_ above 95%. The oxygen flow rate was at least 50L/min in the first 24 h and can be adjusted to 60L/min as needed. The oxygen flow can be reduced to an acceptable level if patients feel uncomfortable. HFNC therapy will last for at least 48 h, then switch to COT.

#### Respiratory training

Respiratory training will be performed using PEP Acapella (Choice), and instruction will be provided by a well-trained physician or respiratory therapist. The specific operation procedures of routine oxygen therapy and videos of respiratory training have already been produced. The implementation of the intervention will be recorded in the Case Report Form.

#### PEP Acapella (choice)

The operation steps are as follow (Patients in the seated or semi-recumbent position):On first use, turn the frequency adjustment dial to the lowest frequency resistance setting marked “1”;Put the nozzle in the mouth, instruct the patient to relax, and then take a deep breath (total lung capacity is not required);Hold breath for 2 ~ 3 s;Exhale slowly, making sure to keep the mouthpiece sealed when exhaling (the exhale time is about 3–4 times longer than the inhale time, no need to exhale forcefully to the “FRC”);Adjust the dial to increase the resistance (adjust clockwise to increase the resistance of the vibrating hole, allowing the patient to exhale at a lower flow rate);Determine the scope;Repeat 10–20 PEP breaths, followed by 2–3 “puff” coughs as needed to cough up secretions; andRepeat the above steps 4 ~ 8 times, no more than 20 min.

Patients can be considered to transfer out of ICU once FiO2 ≤ 35% with SPO_2_ maintained at ≥ 95%.

#### COT group (Group B)

COT would be continued for at least 48 h after extubation and may be continued or stopped after 48 h. Oxygen is transferred through a nasal catheter or a mask (with or without an oxygen storage bag or Venturi system). The oxygen flow is set to maintain SPO_2_ ≥ 95%. Patients can be considered for transfer out of ICU once oxygen flow is < 6L/min with SPO_2_ maintained at ≥ 95%.

### Criteria for discontinuing or modifying allocated interventions {11b}

Participants can withdraw at any time during the trial. And study investigators can decide whether a participant discontinues the trial out of safety concerns, including the following: (1) serious complications such as consciousness disorders; (2) the occurrence of other diseases that affect the efficacy of this trial; and (3) investigators consider the subject unsuitable to continue the study intervention (PEP Acapella).

Other reasons such as death and loss to follow-up may also be considered to terminate the trial. Any modifications of the protocol will be reported to the Ethics Committee and discussed by the study group prior to the implementation.

### Strategies to improve adherence to interventions {11c}

All nurses and physicians involved in this study will be well trained on the specific operation process. Study investigators will visit the participants each day during hospitalization to provide advice on their treatment. Moreover, counsels will also be given on their scheduled clinic visits. Biweekly telephone calls and follow-up at 28^th^ and 1 year after discharge will also be made to improve adherence.

### Relevant concomitant care permitted or prohibited during the trial {11d}

Drugs such as anodyne and expectorant do not affect the trial and can be used according to the guidelines.

### Provisions for post-trial care {30}

Participants will have access to study clinics for post-trial care through the routine health system.

### Outcomes {12}

#### Primary outcome

The primary outcome is the incidence of PPCs within 7 days after surgery. This includes respiratory infections, bronchospasm, aspiration lung injury, pneumonia, atelectasis, pleural exudation, pneumothorax, and acute respiratory failure, according to the EPCO definitions [24]. Each diagnostic criterion is available in the Additional file.

#### Secondary outcome

Secondary outcomes include the following: incidence of PPCs during hospitalization, length of hospital stay, 28-day mortality, NIV or reintubation rates, incidence of surgical complications (surgical site bleeding, infection, wound infection, anastomotic leakage, and surgical reintervention), and all-cause mortality within 1 year.

### Participant timeline {13}

The participant timeline is presented in Table 1.

**Table 1 Tab1:** Flowchart of patient follow-up

			Primary study period		Follow-up		
Timepoint	Screening D − 7 to D − 1	Inclusion D − 1 to D0	D1 to D7 after randomization	End of hospitaliztion	D28 after randomization	D90 after randomization	1Y after randomization
**Enrollments**	×						
Eligibility screen	×						
Patients information	×						
Informed consent	×						
Randomization		×					
**Interventions**							
HFNC		×	×				
Respiratory training		×	×				
COT		×	×				
**Assessments**							
Baseline variables		×					
Laboratory tests Ultrasound, chest radiography		×	×				
Primary outcomes			×				
Secondary outcomes			×	×			
Complication/adverse events			×	×			
Alive or dead status				×	×	×	×

### Sample size {14}

Based on our previous clinical data (the previously mentioned pilot study) and the latest sample size analysis in the literature (nearly 40% incidence of PPCs), we predict that the incidence of PPCs will be approximately 15% lower in Group A than in Group B [7, 18, 25]. PASS.11 software will be used to compute the sample size. Assuming an α value of 0.025, a *β* value of 0.1, with a maximum tolerated patient loss rate of 10%, 164 patients were required per study group.

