### Recruitment {15}

At least 328 patients will be recruited from the Seventh Affiliated Hospital of Sun Yat-sen University through the publication and distribution of text messages, phone calls, and advertisements containing information of the study. Physicians screen potential patients for inclusion and exclusion criteria and register information in the subject registration form. One study investigator checked patients' eligibility for inclusion before randomization.

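### The planned 164 patients per group does not follow from the stated 40% rate, 15-point reduction, α of 0.025, β of 0.1 and 10% loss; it gives about 79% to 83% power, not 90%

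*Protocol article*

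**What the plan says.** All the planning inputs but one are in the protocol article, section Sample size {14}; the allocation ratio is in Trial design {8}.

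- Control rate: the section draws on the pilot study and on "the latest sample size analysis in the literature (nearly 40% incidence of PPCs").
- Effect: "we predict that the incidence of PPCs will be approximately 15% lower in Group A than in Group B".
- Type I error: "Assuming an α value of 0.025", with no statement of whether this is one- or two-sided.
- Type II error, loss and result: "value of 0.1, with a maximum tolerated patient loss rate of 10%, 164 patients were required per study group".
- Allocation: Group A or "the COT group (Group B) in a 1:1 ratio".

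The Abstract and Recruitment {15} carry the result forward as 328 patients in total (2 × 164). Statistical methods {20a} compares categorical outcomes between groups with the chi-squared test. The pilot rates are in Background and rationale {6a}: "The incidence rate of PPCs was 50% (3/6) in the COT group, while the incidence of PPCs was 16.7% (1/6").

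**The concern.** A two-proportion sample size is fixed by the two rates, α, β and the allowance for loss. The article gives a value for each of these and a result, so the result can be checked. A β of 0.1 means 90% power, and 164 per group including loss is low for detecting 40% versus 25% at that power.

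The power claim for the primary endpoint is at stake. It tells a reader how likely the trial is to detect the effect it was built for, and so how much weight a non-significant result can bear. If the true type II error is about twice the stated one, the published design is less sensitive than it says.

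**Working it through.** **Inputs.** Control rate p1 = 0.40 and Group A rate p2 = 0.25, which is the article's control rate with its 15% taken as percentage points; α = 0.025; β = 0.1; loss 10%; allocation 1:1 (Trial design {8}). Sidedness is not stated, so both readings are worked. The normal quantiles are 1.960 (one-sided 0.025, the same as two-sided 0.05), 2.241 (two-sided 0.025), 1.282 (90% power) and 0.842 (80% power).

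**Formula (pooled, matching the chi-squared test).** With mean rate p = (0.40 + 0.25)/2 = 0.325:

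n = [zα √(2p(1−p)) + zβ √(p1(1−p1) + p2(1−p2))]² / (p1 − p2)²

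Here √(2 × 0.325 × 0.675) = 0.6624, √(0.24 + 0.1875) = 0.6538 and (0.15)² = 0.0225.

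**Attempt to reproduce 164 at 90% power.**

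- One-sided 0.025: (1.960 × 0.6624 + 1.282 × 0.6538)² / 0.0225 = 202.8, so 203 evaluable. For loss, 203/0.9 = 225.6, so 226 recruited per group (452 in total).
- Two-sided 0.025: (2.241 × 0.6624 + 1.282 × 0.6538)² / 0.0225 = 239.8, so 240 evaluable. For loss, 240/0.9 = 266.7, so 267 per group (534 in total).
- At one-sided 0.025, the unpooled formula gives 200 (223 with loss) and the continuity-corrected formula 216 (240 with loss).

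None of these is near 164. On the more lenient α the shortfall is 226 − 164 = 62 per group.

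**Power that 164 per group gives.** Power = Φ([0.15 √n − zα × 0.6624] / 0.6538). The evaluable number after 10% loss is 164 × 0.9 = 147.6, taken as 148.

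| Evaluable per group | One-sided 0.025 (two-sided 0.05) | Two-sided 0.025 |
|---|---|---|
| 148 (10% loss) | 79.0% | 69.9% |
| 164 (no loss) | 83.0% | 74.8% |

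For the first cell: 0.15 × √148 = 1.825; (1.825 − 1.960 × 0.6624)/0.6538 = 0.805; Φ(0.805) = 0.790. Exact binomial enumeration of the chi-squared test at 148 per group gives 79.3% and 70.1%, so the approximation is not the cause of the gap.

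**How far other readings of the inputs help** (one-sided 0.025, 90% power).

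- A control rate somewhat under 40%: a 15-point drop from any rate between 35% and 39% still needs at least 205 recruited per group.
- The pilot rates, 50% versus 16.7%: about 41 per group before loss, or up to 54 with two-sided 0.025 and a continuity correction. That is far below 164.
- 15% as a relative reduction (40% to 34%): about 1,359 evaluable per group, far above 164.
- To arrive at about 164 with loss, the control rate would have to be near 27% to 28% with a 15-point drop, or the drop about 17.4 points from 40%. The article states neither.

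**Where 164 may come from.** At 80% power and two-sided 0.05 the unpooled formula gives (1.960 + 0.842)² × 0.4275 / 0.0225 = 149.1, and 149.1 × 1.1 = 164.0. The pooled formula at 80% gives 152, which becomes 168 (× 1.1) or 169 (÷ 0.9).

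**The case against.** The best defence is that the inputs are approximate. The article gives the rate as nearly 40% and the effect as about 15%, cites a pilot with different rates, and does not name the PASS procedure or the sidedness. The pair 40% and 25% is therefore an assumption, and every power figure here depends on it. That is fair. But it is the natural reading and the only one that comes near 164, and the variations worked above do not rescue the number at 90% power.

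A second point is that 10% is described as the maximum tolerated loss, so 79% is the low end. This stands too, and the result should be given as a range. Even with no loss, power is 83% at most by the pooled formula.

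A reader might go further and infer that 164 can only be an 80%-power figure, that β was simply misreported, and that loss was added by multiplying by 1.1 instead of dividing by 0.9. The documents do not support this. The match at 164.0 needs the unpooled formula and an unrounded 149.1; rounding up first gives 150 and then 165. Other unstated routes land as close: 38% versus 23% at 80% power gives 147, and 147/0.9 rounds up to 164; one-sided 0.05 at 90% power with no loss allowance gives about 163 to 166. The number alone cannot identify the faulty input.

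Nor is the relative reading, with its power of about 19%, a fair measure of the problem, because it is nowhere near the stated sample size. And nothing in the article commits the authors to over-reading a null result; the point is only that the stated 90% would mislead a reader who relied on it.

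**Conclusion.** The stated sample size does not follow from the stated inputs. Reading them as 40% versus 25% with 1:1 allocation and a chi-squared test, 164 per group carries a type II error of about 17% to 21% at one-sided 0.025 (two-sided 0.05), or about 25% to 30% if 0.025 is two-sided, against the stated 10%. The lower end of each range assumes no loss and the upper end the full 10%. The more natural reading of 0.025 is one-sided, so about 79% to 83% power is the main result.

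This is an inconsistency among figures the article itself prints, not a detail left to a fuller document. It needs correcting because it is the power claim for the primary endpoint. That the number resembles an 80%-power calculation is a plausible explanation and no more.

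**What to change.** Keep 164 per group and rewrite the paragraph in Sample size {14} so that it states:

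- both planning rates as absolute values, 40% for conventional oxygen and 25% for Group A;
- the sidedness of α: one-sided 0.025, that is, the chi-squared test judged at two-sided 0.05;
- the power delivered, about 79% with 148 evaluable per group after 10% loss, in place of β = 0.1.

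If different inputs were entered in PASS, give those instead, with the procedure used, so that α, β, rates, loss and n agree. If 90% power is truly intended at these rates, the matching figure is 203 evaluable and 226 recruited per group, which is a larger trial and a separate decision.

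Restating costs one paragraph and no additional patients. The downside is a less favourable stated power.
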